#### Illness perceptions

The Brief Illness Perceptions Questionnaire (Brief IPQ) is a nine-item scale designed to assess patients’ cognitive and emotional representations of illness [42]. All items except the causal question are rated on 0 to 10 scale. Five items assess cognitive illness representations: consequences, timeline, personal control, treatment control and identity. Two items assess emotional representations: concerns and emotions. One item assesses illness comprehensibility. The causal representation question asks listing the three most important causal factors of illness. The reliable and valid Brief IPQ is measured at baseline and after 3, 6 and 9 months.

#### Costs

Costs will be measured from a societal perspective using adapted versions of the iMTA Medical Cost Questionnaire (iMCQ) [43] and the iMTA Productivity Cost Questionnaire (iPCQ) [44] including costs of health care utilisation, informal care, and work absenteeism and presenteeism. Medication use will be retrieved from the patient’s pharmacy. If available, Dutch guideline prices will be used to value resource use. Medication use will be valued using prices set by the Royal Dutch Pharmacists Association. Lost productivity costs will be calculated according to the friction cost approach using Dutch mean incomes [45]. According to the friction cost approach a sick employee is replaced after a certain amount of time (the friction period) after which there are no further lost productivity costs [46]. All costs will be adjusted to the year in which most data is collected using consumer price indices.

#### Blood pressure

Systolic and diastolic blood pressure is a clinical secondary outcome and will be measured with an automatic sphygmomanometer in both the intervention and the control conditions according to a standardised protocol. In the intervention condition blood pressure will be measured by the pharmacists at the start of the first consult, at the start of the follow-up consult and at a final pharmacy visit. In the control condition blood pressure will be measured by the pharmacy technician during three pharmacy visits at baseline and after 3 and 6 months. At each visit blood pressure will be measured three times, each 2 min apart, in a seated position.

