### Intervention condition

Patients in the intervention condition will receive the CATI intervention programme in addition to usual care. The programme is a patient-tailored, pharmacist-led, theory-based intervention programme to enhance adherence with the use of antihypertensive medication. It consists of two steps. First, the patients’ barriers to adherence will be identified, and second, tailored information and advice on the identified barriers and specific needs of the patient will be provided. The Self-regulation Theory suggests that patients make an illness and treatment representation which guides their health behaviour. By providing tailored information to the patient regarding the potential risks of high blood pressure and the need for treatment, it is expected to increase patients’ understanding and perceived need to be adherent with their antihypertensive medication. The programme will be executed by the pharmacist and includes two visits to the pharmacy.

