
#### Follow-up consult

Approximately 3 months after the first consult a follow-up consult will be planned with the patient. The purpose of this follow-up consult is to discuss patients’ implementation of and patients’ experiences with the action plan. If needed, the developed action plan of the first consult will be adjusted based upon patients’ experiences.

During the first consult, the follow-up consult and during an additionally planned visit to the pharmacy, patients’ systolic and diastolic blood pressure will be measured with an automatic sphygmomanometer according to a protocol.

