### Statistical analyses

Descriptive statistics will be used to characterise the study population. Dropout and loss to follow-up will also be described. The effect analyses will be performed according to the ‘intention-to-treat’ and ‘per-protocol’ principles. Linear and logistic mixed-model analyses will be used to assess the effect of the intervention programme by comparing the differences between the intervention and the control conditions. Mixed-model analysis is needed in order to take into account clustering on pharmacy level and repeated measurements in one patient. Adjustments will be made for possible confounders such as gender, age and education level. The researcher will be blinded during data analyses.

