The MARS-5 questionnaire has been selected as the primary outcome for this study. Two studies showed poor sensitivity results of the MARS-5 questionnaire [51, 52]. This could be a limitation of this study. An explanation for these results could be the use of the Medication Possession Ratio as a reference standard. This method calculates the extent to which patients refill their medication, rather than calculating the extent to which patients take their medication. Despite these results, the MARS-5 questionnaire has several advantages. First, the questionnaire performs well on other psychometric properties. Second, the response scale allows patients to be graded in terms of the frequency with which they engage in non-adherent behaviours. Third, the questionnaire can distinguish between patients with intentional and unintentional medication non-adherence. Lastly, this questionnaire is relatively short and easy to use. Another limitation of this study is that, due to the nature of the intervention, it is not possible to blind the researcher, patients, pharmacists or pharmacy technicians to the group allocation of participants. To minimise possible ascertainment bias before data collection participants were informed about being randomised into one out of two programmes, with either three blood pressure measurements or two consults and three blood pressure measurements. Moreover, to minimise possible ascertainment bias after data collection, the researcher will be blinded during data analyses. A final limitation of this study is that due to performing the randomisation at the individual level both the intervention and the control conditions will be conducted in one pharmacy which can lead to contamination. To minimise contamination within one pharmacy, the intervention programme and blood pressure measurements will be performed by a pharmacist, whereas the blood pressure measurements in the control condition will be performed by a pharmacy technician; previously, pharmacy technicians had been instructed to perform no activities other than usual care during the three blood pressure measurement visits.

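### In the intervention arm the first two blood pressure readings, including baseline, are tied to attending a counselling consult, which risks differential missingness at those readings

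*Protocol article*

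**What the plan says.** In the protocol article, the Blood pressure section states for the intervention arm that "blood pressure will be measured by the pharmacists at the start of the first consult, at the start of the follow-up consult". The same sentence adds a third reading at a last visit. The Follow-up consult section confirms that this third reading is taken "during an additionally planned visit to the pharmacy", so it is not itself a consult. The Intervention condition section says that the programme "includes two visits to the pharmacy"; these are the two consults, and they are also the visits that carry the first two readings.

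For the other arm the rule is different: "In the control condition blood pressure will be measured by the pharmacy technician during three pharmacy visits at baseline and after 3 and 6 months". According to the Discussion, technicians were told to do nothing beyond usual care at these visits. Participants were told that they would enter one of two programmes, "with either three blood pressure measurements or two consults and three blood pressure measurements".

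On analysis, the Statistical analyses section says: "The effect analyses will be performed according to the ‘intention-to-treat’ and ‘per-protocol’ principles". It plans linear and logistic mixed models and a description of dropout.

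**The concern.** An outcome should be collected from every randomised patient on the same terms, whether or not the assigned treatment is taken up. Here a control patient gives a first and second reading by coming for a short measurement. An intervention patient gives them by coming for counselling. A patient who is willing to be measured but does not want the consult has no reading under the schedule as written.

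All participants were selected for non-adherence on two measures, so it is plausible that those who avoid the consult are also those who take their tablets least and have higher pressure. Their absence would then be related to the outcome and would arise through treatment uptake in one arm only. Blood pressure is a secondary outcome, but it is the only objective clinical outcome listed. The primary outcome is unblinded self-report, and the Discussion acknowledges poor sensitivity results for it, so blood pressure is the natural corroboration.

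**Working it through.** **Step 1: the two schedules side by side.**

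| Reading | Intervention arm | Control arm |
|---|---|---|
| First | Start of first consult, pharmacist | Baseline, technician, blood pressure only |
| Second | Start of follow-up consult, pharmacist | 3 months, technician, blood pressure only |
| Third | Separate final visit, no date given | 6 months, technician, blood pressure only |

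Two of three readings are consult-tied in one arm and none in the other.

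**Step 2: timing of the first reading.** Under Randomisation, the allocation lists go to the pharmacist and the technician once patients have been randomised. Under First consult, the pharmacist then invites the patient. The baseline blood pressure is therefore taken after allocation, at the first treatment visit.

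**Step 3: dependence of the second reading on the first.** The follow-up consult is timed from the first consult. A patient who declines the first consult has no due date for the second reading. The questionnaires, by contrast, are due at baseline, 3, 6 and 9 months and are not linked to consults.

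**Step 4: inputs for an illustration.** The article gives no blood pressure figure to reproduce. Its one computed figure, the sample size for MARS-5, does not bear on this point beyond the total of 156 at 1:1, that is 156 / 2 = 78 per arm. The rest is assumed:

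- q, the share of patients in either arm of the kind who would not attend a consult: 10%, 20% or 30%;
- d, their excess in systolic pressure over attenders: 5 or 10 mmHg;
- c, the share of the control arm with no reading, all from the same kind of patient: 0, q/2 or q;
- no true effect of the programme.

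**Step 5: readings available.** 78 × 0.9 = 70.2, 78 × 0.8 = 62.4 and 78 × 0.7 = 54.6, so about 70, 62 or 55 intervention patients would have a consult-tied reading.

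**Step 6: spurious difference at a consult-tied reading.** Take the attenders' mean as zero. The observed intervention mean is 0. The observed control mean is (q − c)d / (1 − c). Intervention minus control is therefore −(q − c)d / (1 − c).

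| q | c = 0 | c = q/2 | c = q |
|---|---|---|---|
| 10% | −0.5 to −1.0 | −0.26 to −0.53 | 0 |
| 20% | −1.0 to −2.0 | −0.56 to −1.11 | 0 |
| 30% | −1.5 to −3.0 | −0.88 to −1.76 | 0 |

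Values are in mmHg, for d = 5 to d = 10. For example, with q = 0.30, c = 0.15 and d = 10: −(0.15 × 10) / 0.85 = −1.76.

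**Step 7: what the figure measures.** It is a difference in level at one consult-tied reading. If the same patients lack both the first and second readings and their excess is stable, the shift is the same at both, and with c = 0 the change contrast is −qd − (−qd) = 0. The figure is not the bias in a change from baseline, and it does not apply to the final reading.

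**The case against.** A reader might infer that patients who skip the consults drop out of the blood pressure outcome altogether, and that the intention-to-treat comparison becomes one of attenders. The documents do not support that, for four reasons.

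- The third reading is at a separate visit, and nothing excludes a patient who missed the consults from that visit or from the analysis.
- Control readings also require coming to the pharmacy. Poorly motivated control patients may skip visits that offer no counselling, and the single stated loss rate of about 30% is not split by arm. It cannot be assumed that the comparable control patients keep their readings.
- A mixed model uses every available reading and is valid if data are missing at random. The article does not say that a baseline reading is required. Bias needs missingness that is not at random as well as attendance that differs by arm.
- The standardised measurement protocol is not shown, and an article may leave the handling of missed visits to it.

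All four stand, and they limit the point. They do not remove it. The tie between the first two readings and the consults is a stated rule, not a missing detail. For a patient with neither reading, the model has no earlier pressure to condition on, and the covariates named as examples (gender, age, education) do not capture uptake. An analysis plan cannot supply readings that were never taken. The multiple imputation that the article describes is for the economic evaluation.

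**Conclusion.** The point holds in a limited form. Ascertainment of blood pressure is coupled to programme uptake in the intervention arm at the first two of three readings, including the post-randomisation baseline. This risks differential missingness and weakens the intention-to-treat comparison at those readings. It does not show that the intention-to-treat analysis of blood pressure is lost, it does not affect the separate final visit, and it does not touch MARS-5.

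The size is unknown. With 10–30% non-attendance and 5–10 mmHg higher pressure in non-attenders, both assumed, the spurious difference in level at a consult-tied reading lies between 0 (equal loss of comparable control patients) and about 3 mmHg in favour of the programme (no such loss, at the top of both ranges). The upper figure should not be quoted without that condition. For a secondary outcome this is something that should be changed, not something that invalidates the trial.

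**What to change.** In the Blood pressure section, state that the three blood pressure visits are outcome visits due for every randomised patient on one schedule, at baseline, 3 and 6 months, whether or not a consult takes place. Offer an intervention patient who declines or misses a consult a visit for blood pressure only, and analyse that patient in the assigned arm. Record who took each reading and keep the contamination safeguard in the Discussion, under which pharmacists measure intervention patients and technicians measure controls. Sending non-attenders to the technician would cut across that separation and make the measurer depend on uptake within one arm. Report blood pressure availability at each visit by arm and, in the intervention arm, by consult attendance.

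The cost is some wording, extra invitations and a few short visits by staff who already take these readings. Not every non-attender will come. Under Trial status, inclusion had ended by the third quarter of 2016, so the change can affect only visits still outstanding, and baseline readings already missed cannot be recovered. The availability report remains possible in any case.

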### Pilot study

Based on the results of a pilot study the CATI intervention programme was improved and finalised. Ten patients from three community pharmacies participated in the pilot study. These participants filled out the baseline questionnaire and visited the pharmacy for the first consult. Logistics, questionnaires, use of study protocol and intervention materials, and the feasibility of the intervention programme were evaluated. After the pilot study some aspects of the intervention programme were changed, for instance putting more emphasis on the follow-up consult and development of an action plan; simplifying the structure and use of the intervention materials; and adapting logistic aspects to increase feasibility.

### Statistical analyses

Descriptive statistics will be used to characterise the study population. Dropout and loss to follow-up will also be described. The effect analyses will be performed according to the ‘intention-to-treat’ and ‘per-protocol’ principles. Linear and logistic mixed-model analyses will be used to assess the effect of the intervention programme by comparing the differences between the intervention and the control conditions. Mixed-model analysis is needed in order to take into account clustering on pharmacy level and repeated measurements in one patient. Adjustments will be made for possible confounders such as gender, age and education level. The researcher will be blinded during data analyses.

### Sample size

A sample size calculation for proportions has been performed. The sample size is based upon the difference in percentage of adherent participants over 9 months of follow-up between the intervention and the control conditions. A difference of 20% is considered relevant. At baseline, all participants are non-adherent as measured with the self-report adherence questionnaire. The expected percentage of adherent participants (MARS-5 = 25) at the end of the study is 30% for the intervention condition and 10% for the control condition. When using an alpha of 0.05 and a beta of 0.20, a group size of 60 is sufficient, taking the clustered and longitudinal design into account. To adjust for a loss to follow-up of approximately 30%, we will include 156 patients.

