### Study design

A parallel-group randomised controlled trial will be performed in 13 community pharmacies including 156 patients (Fig. 1). Patients will be randomly assigned to the intervention or the control condition. Patients in the intervention condition will receive the CATI intervention programme performed by the pharmacist, in addition to usual care (further described below in 'Control condition'). The effectiveness of the CATI intervention programme will be measured during a 9-month follow-up. See Additional file 1 for an overview of the Standard Protocol Items: Recommendations for Interventional Trials (SPIRIT) 2013 checklist items [26]. See Additional file 2 for the SPIRIT diagram of the trial procedure.

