### Randomisation

To each eligible patient an unique serial number will be assigned. Subsequently, a member of the research team will perform the randomisation process using blocking [28] with a block size of 4, a random cell selection a 1:1 allocation ratio. A list of patients randomised to the intervention or the control condition will be handed to the pharmacist and pharmacy technician, respectively. Blinding of the participants, pharmacists and pharmacy technicians to treatment allocation is not possible due to the nature of the intervention.

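### The 156 patients do not absorb a 30% loss to follow-up: keeping 60 per group needs 172, and 156 is enough only up to about 23% loss

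*Protocol article*

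**What the plan says.** The Sample size section of the protocol article plans for an expected proportion of adherent patients that "at the end of the study is 30% for the intervention condition and 10% for the control condition", and adds that "A difference of 20% is considered relevant". It continues: "When using an alpha of 0.05 and a beta of 0.20, a group size of 60 is sufficient". The same sentence says that this group size already allows for clustering and repeated measurement. The next sentence makes the allowance for loss: "To adjust for a loss to follow-up of approximately 30%, we will include 156 patients".

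The Randomisation section specifies "a 1:1 allocation ratio", so 60 per group means 120 in total. The Study design section repeats the total: "A parallel-group randomised controlled trial will be performed in 13 community pharmacies including 156 patients". No other section gives a different loss rate or another reason for 156.

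**The concern.** A loss rate applies to the patients enrolled. The number to enrol is therefore the number needed at the end divided by the proportion retained. Multiplying the number needed by one plus the loss rate gives too few, and 156 is exactly what that multiplication produces from 120 and 30%.

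What is at stake is a stated property of the design. A reader would take it that the trial can lose 30% of its patients and still have 60 per group. The Statistical analyses section says that loss to follow-up will be described, so the observed loss will be compared with the stated allowance. The allowance that 156 supports is about 23%, not 30%.

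**Working it through.** **Inputs** (Sample size section unless stated): alpha 0.05; power 0.80; 30% v 10%; 60 per group; loss about 30%; total 156 (also in Study design); 1:1 allocation (Randomisation). The article does not say whether alpha is one- or two-sided. Two-sided is assumed here, and it reproduces the group size closely.

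**1. The plan's group size.** Standard two-proportion formulas, with no design effect, give:
- unpooled variance: (1.960 + 0.842)² × (0.21 + 0.09) / 0.20² = 58.9, so 59 per group
- arcsine: 59.01, so 60 per group
- pooled variance: 62 per group

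The stated 60 is reproduced to within two patients. It shows no visible reserve that could cover a larger loss.

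**2. The plan's total.**
- 120 × (1 + 0.30) = 156, which matches exactly
- 120 / (1 − 0.30) = 171.4, so 172 (86 per group), which is 16 more than 156

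**3. What 156 leaves at 30% loss.**
- 156 × 0.70 = 109.2 patients, or 54.6 per group
- shortfall against 120: about 11 patients

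**4. The loss that 156 can absorb.**
- 1 − 120/156 = 36/156 = 23.1%

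**5. Power at 54.6 per group, if lost patients contribute nothing.**
- Scaled from the plan's own anchor (60 per group gives 80%): Φ(2.8016 × √(54.6/60) − 1.960) = Φ(0.713) = 76.2%
- Unpooled formula: Φ(√(54.6 × 0.04/0.30) − 1.960) = Φ(0.738) = 77.0%; the same formula gives 80.7% at 60
- Pooled formula: Φ((0.20 × √54.6 − 1.960 × √0.32) / √0.30) = Φ(0.674) = 75.0%; the same formula gives 78.9% at 60

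Each method shows a drop of about 4 percentage points. Part of the gap between 75.0% and 80% is not due to loss, because the pooled formula needs 62 per group to begin with.

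**6. Range over the loss rate.**

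| Loss | Left per group from 156 | Power, scaled from 60 = 80% | Power, pooled formula | Enrolment that keeps 120 |
|---|---|---|---|---|
| 25% | 58.5 | 79.0% | 77.9% | 160 |
| 30% | 54.6 | 76.2% | 75.0% | 172 |
| 35% | 50.7 | 73.1% | 71.8% | 185 |

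**The case against.** **Partial data.** This is the strongest objection. MARS-5 is measured at 3, 6 and 9 months, the analysis is a mixed model with repeated measurements, and the sample size refers to the difference over the whole follow-up. A patient lost after month 3 or 6 still contributes. A reader might infer that the trial simply has 76% power. The documents do not support that: the figure holds if every lost patient leaves before giving any follow-up data. The objection limits the consequence but does not reconcile the numbers. The article says that the 60 already reflects the longitudinal design, and it then makes a separate allowance for loss.

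**Choice of formula.** A reader might also take 76% as independent of the method used. It is not. It assumes exactly 80% at 60 per group, and direct formulas give 75.0% and 77.0%. The calculation behind the 60 is not shown, so the true figure could differ. For example, a net design effect above 1 that the 60 does not cover would lower it.

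**Origin of 156.** It is tempting to say that the authors multiplied by 1.3. The article does not show this step. The total is also 13 pharmacies × 12 patients, and 12 is three blocks of 4, although the article does not give that derivation either. The mismatch is the same whichever route was taken.

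**Looseness of the loss rate.** The article says that the loss is approximate. That does not comfortably stretch from 30% to 23%. Even at 25% loss fewer than 60 per group remain.

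**Importance.** About 4 points of power is a small effect. It has no bearing on the validity of the estimate or on the type I error rate, and the Trial status section says that inclusion has ended. This stands, and it makes the point a correction of a reported figure rather than a flaw that threatens the trial.

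**Conclusion.** The sentence is wrong as written. The figures of 60 per group, about 30% loss and 156 enrolled cannot all hold. At 30% loss, 156 leaves about 109 patients (about 55 per group), and keeping 60 per group would need 172. The stated total covers a loss of at most about 23%. This part rests only on the article's own numbers and on equal allocation.

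The effect on power is modest and conditional: about 76% instead of 80% at 30% loss (75% to 77% by direct formulas). It assumes a two-sided alpha, that 60 per group truly gives 80%, and that lost patients contribute no data. Partial follow-up in the mixed model may reduce the shortfall. The documents do not support going further and calling the trial invalid or materially underpowered.

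**What to change.** Replace the sentence on loss to follow-up with wording such as: *156 patients leave 60 per group if loss to follow-up is at most about 23%; at 30% loss about 55 per group complete, and power is about 76% if lost patients contribute no data and 60 per group gives 80%.*

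The Study design section can keep 156 as the number included. The cost is one sentence and a slightly less favourable power figure. No further enrolment and no change to the analysis are needed.
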